**Methods/Design:**

The trial, randomised, multi-center, evaluator-blinded, parallel group controlled, is designed according to CONSORT Statement. Eligible subjects are infants born preterm without major complications, aged 3-9 months of corrected age with specific gross-motor abilities defined by Ages & Stages Questionnaire scores. Recruited infants, whose parents will sign a written informed consent for participation, will be randomized in CareToy training and control groups at baseline (T0). CareToy group will perform four weeks of personalized activities with the CareToy system, customized by the rehabilitation staff. The control group will continue standard care. Infant Motor Profile Scale is the primary outcome measure and a total sample size of 40 infants has been established. Bayley-Cognitive subscale, Alberta Infants Motor Scale and Teller Acuity Cards are secondary outcome measures. All measurements will be performed at T0 and at the end of training/control period (T1). For ethical reasons, after this first phase infants enrolled in the control group will perform the CareToy training, while the training group will continue standard care. At the end of open phase (T2) all infants will be assessed as at T1. Further assessment will be performed at 18 months corrected age (T3) to evaluate the long-term effects on neurodevelopmental outcome. Caregivers and rehabilitation staff will not be blinded whereas all the clinical assessments will be performed, videotaped and scored by blind assessors. The trial is ongoing and it is expected to be completed by April 2015.

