### Study design

A multicenter, evaluator-blinded, parallel group RCT will be carried out to compare the effects of the CareToy training to standard care in preterm infants.The two clinical centres involved in the study are the IRCCS Fondazione Stella Maris, Department of Developmental Neuroscience, in Pisa (Italy), in collaboration with Neonatal Intensive Care Unit, Pisa University Hospital “Santa Chiara” and in Copenhagen (Denmark) the Helene Elsass Center, in collaboration with the University of Copenhagen (Depts. of Neuroscience and Pharmacology and Neonatology, Rigshospitalet). Clinical assessment will be performed at baseline (T0, in the week preceding the CareToy intervention/standard care) and in the week after the end of CareToy training/standard care (T1, primary endpoint). For ethical issues, after T1, the infants who start with standard care will have the opportunity to receive the CareToy training, while the infants that have already performed CareToy training will continue standard care. At the end of this open phase (T2), all the infants will be assessed as at T1. Moreover, a further assessment will be performed at 18 months of corrected age (T3) to evaluate the long-term effects on neurodevelopmental outcome. The experimental design and the timeline are described in detail in Figure 2. A pilot study has been performed in order to assess the feasibility of the CareToy training and to tune and set-up the CareToy system and the rehabilitation packages.

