### Therapy protocols

#### CareToy training

On the base of each infant’s developmental needs, the rehabilitation staff (e.g. child neurologists and paediatric physical therapists) will plan a series of individualized goal-directed activities (rehabilitation packages) mainly focused on postural control, reaching, grasping, manipulation, visual attention and orientation in supine, prone and/or sitting position. According to the planned activities, the CareToy system will be personalized and delivered at the home of the infant. The CareToy training will be used daily for 4 weeks (28 days). Each daily training lasts about 30-45 minutes and consists of various activities of 2-10 minutes duration performed during the day when the infant is in active state and compliant.

Daily training will be remotely monitored by the rehabilitation staff, who may modify the rehabilitation packages according to infant’s developmental needs and progress. Caregivers will fill out a questionnaire at the end of each training session to record acceptance and compliance to the activities by the infant. The drop-out criterion for each daily session is if the infant completes less than 51% of the planned scenarios.

Caregivers will be trained in playing with their infant through the CareToy system during the first training week by the rehabilitation staff. In the following 3 weeks of training, support and advice will be given, even on site if necessary.

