### Primary outcome measure

#### Infant Motor Profile (IMP)

It is a new, video-based and qualitative assessment of motor behaviour in infancy, applicable in preterm and at term infants aged 3 to 18 months [33]. It consists of 80 items addressed to explore the child's motor abilities and to evaluate motor behaviour in five domains: i) variation, ii) variability (ability to select motor strategies), iii) movement fluency, iv) movement symmetry and v) motor performance.

IMP consists of spontaneously and elicited motor behaviour recording while the infants are in supine, prone, sitting, standing, walking (depending on infants' age and functional capacity), reaching, grasping, and manipulation of objects in supine and in supported sitting positions. The assessment lasts approximately 15 minutes. The total IMP score is constituted by the mean of the five domain scores. It is scored off-line on the basis of the video recordings.

This tool is intended to detect and quantify changes after intervention and it is reported as having a satisfactory intra and inter-observer reliability and a good score reliability. In particular, it has been demonstrated that the inter-observer reliability of the total IMP score yielded an ICC of 0.94 (95% CI 0.87–0.97), and the reliability of scoring the IMP domains moderate to good, with ICCs ranging from 0.69 to 0.99. Moreover a strong correlation between IMP performance domain score and AIMS has been found [33, 34]. This evaluation will be carried out at all four time-points (T0-T3), but only the change from T0 to T1 will be used as the primary outcome.

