### Analyses

Clinical Data will be managed and analysed using the Statistical Package for Social Sciences (SPSS). Descriptive statistics (means, standard deviation) will be calculated to summarise the data set for both groups and to identify potential baseline differences between the groups; p values will be used to indicate the strength of the evidence, and the Bonferroni correction for multiple assessments will be performed. The primary level of analysis will be the assessment of the effects of CareToy training at the primary endpoint (T1) in the primary and then in the secondary outcome measures. In the second level analysis we will provide multivariate statistics in order to take into account effect modifiers such as basal level of motor development, family compliance and time of training.

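### Family compliance and amount of training arise after randomisation and have no counterpart in controls before T1, so the second-level analysis cannot treat them as modifiers of the randomised effect

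*Protocol article*

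**What the plan says.** The Analyses section sets two levels. The primary level compares the groups at T1, first on the primary and then on the secondary outcomes. The second level uses "multivariate statistics in order to take into account effect modifiers such as basal level of motor development, family compliance and time of training". One baseline variable and two other variables are thus put in the same class.

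Four other places in the article bear on this:

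- **Abstract, Methods/Design**, on the period up to T1: "The control group will continue standard care".
- **Study design**: "after T1, the infants who start with standard care will have the opportunity to receive the CareToy training".
- **CareToy training**: "Caregivers will fill out a questionnaire at the end of each training session to record acceptance and compliance to the activities by the infant". Activities are "performed during the day when the infant is in active state and compliant", and staff may change the packages as the infant progresses.
- **Infant Motor Profile (IMP)**: "only the change from T0 to T1 will be used as the primary outcome".

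No compliance or training-time measure is described for standard care. The article does not define time of training and does not say how family compliance is measured. The session questionnaire concerns the infant's acceptance and compliance.

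**The concern.** An effect modifier of a randomised contrast must be defined for every infant regardless of allocation, and is best measured before it. Compliance with CareToy and amount of CareToy training meet neither condition over T0 to T1, the interval of the primary outcome. They follow from allocation, and control infants have nothing to comply with.

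They may also be tied to prognosis. Sessions take place when the infant is alert and willing, and the programme follows the infant's progress. Infants who complete more may be those who would have developed faster anyway. The article gives no data on this, so it is a plausible risk and not a demonstrated fact.

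What is at stake is how a secondary result is read. In a trial of about 36 evaluable infants, a group effect adjusted for compliance could be taken to confirm or contradict the primary comparison when it estimates something else.

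**Working it through.** **Inputs from the article.** Target difference 7.5 IMP points, SD 8.2, 36 infants before drop-out, 40 recruited (Sample size); 1:1 allocation (Randomisation); training planned for 28 days (CareToy training).

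**The plan's own figure.** The usual two-sided formula gives 2 × (1.960 + 0.842)² × 8.2² / 7.5² ≈ 18.8, so 19 per arm or 38 in total, within 2 of the stated 36. Then 36 / 0.9 = 40. The point does not concern sample size; 18 per arm is used below only for scale.

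**Step 1: can modification by dose be estimated?** Let g = 1 for CareToy and 0 for control, and let d be dose or compliance up to T1. Controls all have the same value k (naturally 0). Then d = k − k·g + g·d, so the columns 1, g, d and g·d are linearly dependent for any k. The design has rank 3 of 4. There is no slope in controls to compare with the slope in trained infants. If every trained infant completes exactly 28 days, the columns 1, g and d have rank 2 of 3, and group and dose cannot be separated at all. Neither result needs an assumption about how compliance is distributed.

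**Step 2: what does the group coefficient mean if d is only a covariate?** With controls at 0, least squares gives

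adjusted group coefficient = (ȳ₁ − ȳ₀) − b·d̄₁,

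where b is the slope of outcome on dose within the CareToy arm and d̄₁ is that arm's mean dose. This is the predicted difference for a CareToy infant with zero dose. The slope b mixes any true dose-response with any link between compliance and prognosis.

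**Step 3: illustration of scale (assumptions, not estimates).** Suppose compliance has mean m and SD s in the trained arm and correlation ρ with the infant's own prognosis, with no true dose-response. Treat 8.2 as the outcome SD. The expected shift is about −ρ × 8.2 × m / s.

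| m | s | ρ | Expected shift (points) |
|---|---|---|---|
| any | any | 0 | 0 |
| 0.80 | 0.12 | 0.3 | −0.3 × 8.2 × 6.67 = −16.4 |
| 0.80 | 0.12 | 0.5 | −0.5 × 8.2 × 6.67 = −27.3 |
| 0.75 | 0.25 | 0.5 | −0.5 × 8.2 × 3 = −12.3 |
| 0.75 | 0.17 | 0.5 | −0.5 × 8.2 × 4.41 = −18.1 |
| 0.75 | 0.10 | 0.5 | −0.5 × 8.2 × 7.5 = −30.8 |

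A simulation (10,000 trials per setting, 18 per arm, m = 0.80, s = 0.12, dose capped at 28 days, true effect 7.5) agrees. The adjusted coefficient averaged 7.4, −9.3 and −20.6 at ρ = 0, 0.3 and 0.5, while the unadjusted difference averaged 7.5 throughout. At ρ = 0 there is no bias, but the empirical standard error rises from 2.7 (by formula 8.2 × √(2/18) = 2.73) to 14.6.

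**Step 4: dependence on coding.** Replace d by d − d̄₁ in the trained arm and leave controls at 0. The fitted values are the same, but the term b·d̄₁ drops out and the group coefficient equals ȳ₁ − ȳ₀ exactly. The shifts in Step 3 therefore belong to one parameterisation. The rank result in Step 1 does not.

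**The case against.** The strongest reply is that the article never specifies the model criticised here. It does not say that the second level is a between-arm regression at T1, or that controls are coded zero. T1 is tied explicitly to the primary level only. A dose-response analysis confined to trained infants would fit the sentence, and an article may leave model detail to a fuller document. This stands as a limit: the bias in Step 2 is conditional on a between-arm covariate model. It does not remove the point, because the sentence classes compliance with a genuine baseline modifier and does not confine it to trained infants.

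Three further points stand in part.

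- **Time of training is undefined.** Entry spans 3 to 9 months corrected age, and the ASQ-3 section uses the questionnaire to choose each infant's starting time. If the term means age at start, it is in effect age at T0 and legitimate. Family compliance remains a problem either way.
- **Controls may train after T1.** Compliance could then exist in both sequences by T2 and be analysed in pooled trained infants. It would still be post-randomisation, and the randomised comparison with untrained infants has ended by then.
- **Family compliance is not shown to be the session questionnaire,** which concerns the infant. However it is measured, no pre-T1 counterpart in controls is described.

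A reader might infer that the trial's treatment effect as such is biased or not estimable, or that including compliance costs a definite number of IMP points. The documents support neither. The primary comparison uses none of these variables, and Step 4 shows that the shift vanishes under another coding of the same model.

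**Conclusion.** The point holds for the second-level analysis. Family compliance, and time of training if it means amount of training, cannot be estimated as modifiers of the randomised T0-T1 effect. That follows from the design alone, since controls have no CareToy sessions before T1.

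A group coefficient adjusted for them with controls at zero is an extrapolation to zero compliance. It is imprecise in any case, and biased if compliance is related to prognosis. The illustrative shifts run from 0 to about −31 points on assumed inputs and uncentred coding. That range shows only that the risk can be large beside the 7.5-point target; no figure within it should be cited as the bias.

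Baseline motor level is a sound choice, and the primary T1 comparison is not affected. The wording should be corrected, but the trial's main inference does not depend on it.

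**What to change.** Reword the second-level sentence in the Analyses section as follows.

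1. Limit modifiers and covariates in between-arm models to variables fixed before randomisation: T0 IMP, corrected age at T0 and centre.
2. Take family compliance and amount of training out of those models. Report them descriptively, and analyse them only among trained infants as an exploratory dose-response analysis labelled non-randomised. Alternatively, estimate a complier-average effect with allocation as the instrument, with the definition of a complier and the assumptions stated beforehand.
3. Define both terms and say how family compliance is measured. If *time of training* means age at start, replace it with *corrected age at T0*.

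The cost is analysis wording only. Data collection, sample size and conduct do not change, and the compliance data remain in use.

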## Discussion

The paper presents the background and the design for a RCT comparing a new intervention, CareToy Home, with the standard care for infants at low risk for neurodevelopmental disorders.

The study is the first to test this new type of treatment as a new tool for an intensive, individualized, home-based and family-centred intervention, managed remotely by clinical staff. The present research aims to assess the feasibility of the system and determine its effect on the neurodevelopment of a group of preterm infants at low risk for neurodevelopmental disorders. If successful, a future aim is to apply the system in further studies involving infants at higher risk for brain lesion or genetic disorders. The CareToy Home system represents a challenging and innovative tool in the field of infant rehabilitation.

This trial will explore the applicability of a new frontier of tele-medicine in infants. This opens the possibility of managing early intervention in infants at home from the clinical centre, expanding the access of infants to EI. Moreover, the rigorous scientific design, according to CONSORT guidelines [26, 27] will allow us to evaluate the effects of CareToy training on neuro-developmental outcome in a first sample of at low risk preterm infants.

## Abbreviations

AIMS: Alberta infant motor scale
ASQ-3: Ages & stages questionnaire – 3
BSID-III: Bayley scales of infant development – III
CI: Confidence interval
CONSORT: Consolidated standards of reporting trials
EE: Enriched environment
EI: Early intervention
EU: European Union
EC: European Conformity
GMA: General Movement Assessment
HINE: Hammersmith neurological examination
ICT: Information and communication technologies
IMP: Infant motor profile
IVH: Intra-ventricular Haemorrhage
NICU: Neonatology Intensive Care Unit
PSI: Parenting stress index
PVL: Periventricular leukomalacia
RCT: Randomised controlled trial
SD: Standard deviation
SPSS: Statistical package for social sciences
VLBW: Very low birth weight.
